### Recruitment

Since in PHC centers the Alcohol, Smoking, and Substance Involvement Screening Test (ASSIST) is applied routinely—in preventive check-ups—to individuals aged 20-65 years, the staff members responsible for applying this test at each PHC clinic will invite individuals whose scores are equal to or higher than 11 on the ASSIST for alcohol and 4 for other substances to participate in this study. If they accept, they will be given an appointment with the research coordinator or a research assistant, who will formally invite them to participate.

The inclusion criteria are as follows: participants must have an ASSIST score of 11 or higher for alcohol and a score of 4 or higher for other substances, be able to communicate verbally with others, be willing to participate in the intervention, and be willing to complete the measurement instruments.

The exclusion criteria are as follows: participants with a severe and untreated mental illness such as schizophrenia, those not willing to participate in the intervention, those not willing to complete the measurement instruments, those who have received another brief intervention within the last year, and those currently being treated in another program for substance use will not be eligible to participate.

### Interventions for Control and Experimental Groups

For the control group, the intervention will be 1 brief counseling session and an educational brochure, provided as part of usual care in PHC. Our team has provided the practitioners participating in this study with a guideline to conduct this brief counseling based on the recommendations of the World Health Organization (WHO) [37]. These materials can be requested from the first author.

For the experimental group, the intervention will be a 3-session brief intervention based on solution-focused practices, implemented by trained social workers or psychologists, who will receive 24 hours of training provided by this study. Our team has designed a manual with the goals and structure of each session, main interventions, and examples of application in different situations. The manual can be requested from the first author. The fidelity of this intervention will be monitored through the application of the Fidelity Instrument [38] to 5 audio recordings of sessions per practitioner participating in the program. This adapted instrument, used in a previous study by the research team [32], contains techniques and skills that professionals should implement in SFBIs. It consists of 13 items with binary responses (1=yes and 0=no). In addition, once the recruitment of participants starts, practitioners in this study will participate every 2 weeks in a 1-hour group consultation meeting, where a master’s in clinical social work with advanced training in SFBIs will supervise the group in the application of SFBI techniques—focusing on best practices, solving questions, reviewing difficulties, and strengthening adherence of practitioners.

### Data Collection

The protocol for participants’ invitations begins once the patient is eligible (Figure 1). The practitioner who detects an eligible participant in the PHC will conduct usual care, consisting of a brief counseling intervention of 10-15 minutes, focused on providing advice and an educational brochure with information about the risks of substance use. Following that, the practitioner will invite the potential participant and inform them regarding the implications of participating in this study, including the set instruments to complete, the possibility of receiving 3 SFBI sessions or only the brief counseling already provided, and the voluntary nature of their decision to participate. If the potential participant agrees to participate in the study, both participant and practitioner will read and sign the informed consent form. Neither of them will know which group the participant will be assigned to at this stage.

### Instruments

#### Background Information

This includes age, gender, socioeconomic status, education level, employment status, county of residence, and family situation (relationship status, children, and their ages). This information is relevant for documenting and accounting for the heterogeneity or homogeneity of the study’s participants and will serve as control variables for data analysis. This instrument will be administered completely at baseline and at the 9-month follow-up and partially (employment status and county of residence) at the 3- and 6-month follow-up, to visualize changes in sociodemographic variables and the identification of protective and change factors during the process.

#### ASSIST

This 8-item questionnaire developed by the WHO, is used to detect risk in substance use [37]. It predicts low, intermediate, and high risk due to substance use. It is a relatively new instrument, recently validated in Chile and recommended by the WHO for assessing risk in alcohol and substance use. The validation in Chile [40] considers a score equal to or greater than 11 for intermediate to high-risk alcohol consumption and a score equal to or greater than 4 for intermediate to high-risk substance use. It is one of the main dependent variables of the study and will be administered at baseline and follow-ups.

#### Treatment Outcome Profile

This instrument has been validated in Chile [41] and was originally developed by the National Treatment Agency for Substance Misuse [42]. It is used to obtain comparable data and goals regarding improvements of individuals with substance use after treatment. It consists of 3 sections: substance use in the past 4 weeks, offensive behavior (social norms such as theft, drug dealing, fights, and domestic violence), and physical and psychological health, including quality of life, work, education, and housing. In total, there are 17 questions. It will be administered at baseline and follow-ups.

#### Patient Health Questionnaire-9

This self-administered 9-item instrument, used in primary care settings, corresponds to the depression module of the Primary Care Evaluation of Mental Disorders, which identifies various mental health disorders [43]. It reflects the 9 symptoms of depression from the *DSM-IV* (*Diagnostic and Statistical Manual of Mental Disorders* [Fourth Edition]). It has high convergent validity (*r*=0.73; *P*<.001) with the short version of the Beck Depression Inventory in detecting depression severity [44]. It has been validated in the Chilean population by Baader et al [45]. It will allow the observation of depressive symptoms prevalence in individuals using different types of substances at baseline and follow-ups, as well as exploring the association between them.

#### Generalized Anxiety Disorder-7 Scale

This is a self-report instrument to assess generalized anxiety disorder (GAD), based on GAD symptoms from DSM-IV. In primary care, its construct validity showed strong correlations between the Generalized Anxiety Disorder-7 (GAD-7) scale’s severity scores and worsening function on all 6 Health-Related Quality of Life scales of the Medical Outcomes Study Short-Form General Health Survey, as well as a high internal consistency (Cronbach α=0.92) [46]. This instrument was adapted for the Chilean population by Crokett et al [47]. It consists of 7 items with 4-point ordinal responses, with 0 indicating never and 3 indicating almost every day. This instrument will allow for the observation of the prevalence of anxiety symptoms in individuals who use different types of substances at baseline and follow-ups, as well as the exploration of associations between these factors.

#### Motivation and Treatment Needs Scale

This scale, developed by Joe et al [48], is part of the Client Evaluation of Self and Treatment, a comprehensive instrument consisting of 147 items grouped into 16 scales. In this study, 2 subscales will be used: Help-seeking Desire and Treatment Readiness [49]. Together, these subscales comprise 14 items with responses on a Likert-type scale, where 1=strongly disagree and 5=strongly agree.

#### Focus Group Guides

Guidelines for these focus groups, to be conducted with the psychosocial teams and participants from the intervention group, were designed specifically for this study to explore participants’ perceptions regarding the implementability of the SFBI model for substance use in PHC contexts (Multimedia Appendix 2).

The quantitative instruments (background information, including demographic data and sociofamilial situation, ASSIST, treatment outcome profile (TOP), Patient Health Questionnaire-9 (PHQ-9), GAD-7, and desire for help and treatment readiness form) will be administered in a private room at the health care center or over the phone (depending on coordination with each patient) by the research coordinator or a research assistant. The estimated time for administering the instruments is 25 minutes per set. The qualitative instruments (focus groups for practitioners and participants) will be implemented after the implementation process has concluded, and conversations will last between 60 and 90 minutes.

Following the informed consent procedures, the instruments will be administered on 4 occasions (Table 1).

**Table 1 table1:** Outline for application of instruments per participant.

Instrument	Baseline	3-month follow-up	6-month follow-up	9-month follow-up	After finishing follow-ups
Background information	✔			✔	
TOP^a^	✔	✔	✔	✔	
PHQ-9^b^	✔	✔	✔	✔	
GAD-7^c^	✔	✔	✔	✔	
Desire for help and treatment readiness	✔				
Focus group					✔

^a^TOP: treatment outcome profile.

^b^PHQ-9: Patient Health Questionnaire-9.

^c^GAD-7: Generalized Anxiety Disorder-7.

### Safeguarding Mental Health

Regarding mental health well-being, this SFBI focuses on positive aspects and the future, minimizing the risk of causing any harm to mental health. If a patient feels distressed or uncomfortable during an intervention session, professionals trained in SFBIs will also be trained to contain and intervene in crises. This additional training, separate from SFBI training, will consist of a 2-hour training session on psychological first aid, provided by an expert hired for that purpose. Furthermore, the research team will ensure that the health clinic has a mental health protocol in place for its regular care. Additionally, the research coordinator and the principal researcher will be available if required. If, during follow-up procedures or any health assessment, a study participant is identified as being at risk and requiring a different type of clinical intervention, the health care team will notify the research team regarding the participant’s continued involvement in the study. In all cases, clinical decisions will take precedence over research participation.

### Analysis Plan

For quantitative-specific objective 3, we will use the standard *P*<.05 criterion to make inferences. Tests to detect any potential differences between individuals who received interventions from either social workers or psychologists will be conducted. The analysis approach for each specific objective is described in the following sections.

#### Specific Objective 1

The first specific objective aims to determine whether the SFBI reduces substance use patterns and risk-level substance use of participants at the 3-month, 6-month, and 9-month follow-ups (post baseline). A descriptive analysis of the recorded variables will be conducted for each participant in the experimental group, pretreatment, and at 3 months, 6 months, and 9 months post baseline. Minimum and maximum values will be reported, and the normality of their distribution will be assessed using frequency histograms and the Shapiro-Wilk normality test. Categorical variables will be described using absolute and percentage frequencies. For individuals participating in the experimental group, the following analyses will be conducted separately at each posttreatment measurement (3 months, 6 months, and 9 months): the change in frequency and quantity of consumption according to the TOP instrument will be calculated for each participant, with the mean change and its corresponding CI estimated, and a paired repeated-measures ANOVA conducted to evaluate whether there is a significant treatment effect on the average weekly consumption; if the normality assumption is not met, the nonparametric Wilcoxon signed-rank test will be used. In addition, the percentage of individuals who decrease their risk category will be calculated, and their respective CIs estimated, and, since the TOP contains categorical items, the McNemar test will be applied to evaluate whether significant changes occurred.

#### Specific Objective 2

The second specific objective aims to determine whether the SFBI reduces consequences of substance use and improves mental health symptoms of participants at the 3-month, 6-month, and 9-month follow-ups (post baseline). For individuals participating in the experimental group, the following analyses will be conducted for each postbaseline measurement (3 months, 6 months, and 9 months): the scores obtained on the PHQ-9 instrument will be calculated and described using mean, SD, median, minimum, and maximum values, and the distribution normality will be assessed using frequency histograms and the Shapiro-Wilk normality test. The change in the PHQ-9 questionnaire score and the desire for help and treatment-readiness scales will be calculated, the means with their corresponding CIs will be estimated, and a repeated-measures ANOVA will be conducted to evaluate whether there is a significant treatment effect on each score.

#### Specific Objective 3

The third specific objective aims to determine whether participants receiving the SFBI improve their substance use patterns, substance use risk level, consequences of substance use, and mental health symptoms as compared with those receiving a minimal intervention. A descriptive analysis of the recorded variables will be conducted for each participant in both experimental and control groups at baseline and at 3 months, 6 months, and 9 months post baseline. Quantitative variables will be described using mean, SD, median, minimum, and maximum values, and their distribution normality will be assessed using frequency histograms and the Shapiro-Wilk normality test. Categorical variables will be described using absolute and percentage frequencies. For each posttreatment measurement (3 months, 6 months, and 9 months), the following analyses will be conducted: the change in substance use patterns and substance use risk level (TOP) will be calculated for each participant in both experimental and control groups, and the mean with its corresponding CI will be estimated; the change in the PHQ-9 score will be calculated for individuals in both experimental and control groups, and the mean with its corresponding CI will be estimated; the change in the GAD-7 score will be calculated for individuals in both experimental and control groups, and the mean with its corresponding CI will be estimated. Baseline characteristics, including demographic background and sociofamilial situation, of participants in the control and experimental groups will be compared, with *t* tests or Wilcoxon-Mann-Whitney tests used for quantitative variables when the normality assumption is unmet, and the Fisher exact test used for categorical variables. Given that this is a superiority design, 1-tailed tests will be used for the following comparisons. The mean decrease in monthly consumption will be compared between individuals in the experimental and control groups using a mixed ANOVA, with group (experimental and control) as the between-subjects factor and time of measurement (pretreatment, 3 months, 6 months, and 9 months) as the within-subjects factor. Similarly, mean PHQ-9 scores will be compared between the two groups using a mixed ANOVA, with group (experimental and control) as the between-subjects factor and time of measurement (pretreatment, 3 months, 6 months, and 9 months) as the within-subjects factor, with the Friedman-aligned ranks test applied if the variable normality assumption is unmet. Finally, the percentage of individuals who decrease their substance use patterns and risk (TOP) will be compared between the experimental and control groups, using the Fisher exact test.

#### Specific Objective 4

The fourth specific objective aims to explore whether psychosocial professionals implementing the SFBI and the individuals who participated in the intervention group find that the model is acceptable and relevant to primary care. The transcribed focus groups will be analyzed using content analysis methodology to identify the concepts and themes in the transcribed data. Initially, the concepts appearing in the texts will be recognized and grouped into themes. According to Hsieh and Shannon [50], content analysis can be approached in two ways. The first is a deductive strategy, with predefined thematic categories established by the researchers based on the goals of the analysis or previous theories. The second is an inductive strategy, without predefined categories, as these are constructed based on the findings, maintaining conceptual openness for analysis. In this case, both strategies will be combined, using the predefined categories of acceptability and relevance of the SFBI from the perspective of professionals and individuals, while remaining open to other new categories or concepts emerging in the focus group conversations.

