### Hypotheses

This study has the following hypotheses. First, participants who receive the SFBI will decrease their substance use patterns and risk-level use of alcohol, marijuana, cocaine, and cocaine base paste. Second, participants receiving the SFBI will report positive changes in the consequences associated with alcohol, marijuana, cocaine, and cocaine base paste use, as well as improvements in mental health symptoms between baseline and follow-ups. Third, when comparing outcomes between the intervention group and the usual care group, it is expected that participants in the intervention group will show greater reductions in substance use, consequences of use, and mental health symptoms than those receiving usual care. Finally, both participants and professionals involved in the intervention group will report experiences indicating that the model is acceptable and relevant for implementation in primary care.

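### Objectives 1 and 2 test before-after change in the SFBI arm alone and read it as a treatment effect, which that change cannot establish

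*Protocol article*

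**What the plan says.** The Analysis Plan words Objective 1 causally: "The first specific objective aims to determine whether the SFBI reduces substance use patterns and risk-level substance use of participants". The population is then restricted: "For individuals participating in the experimental group, the following analyses will be conducted separately at each posttreatment measurement". Within that arm, change in consumption is tested by "a paired repeated-measures ANOVA conducted to evaluate whether there is a significant treatment effect on the average weekly consumption", with a Wilcoxon signed-rank test if normality fails. For risk category, "the McNemar test will be applied to evaluate whether significant changes occurred".

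Objective 2 keeps the restriction to the experimental group. For the PHQ-9 and the help and readiness scales, "a repeated-measures ANOVA will be conducted to evaluate whether there is a significant treatment effect on each score".

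The Hypotheses section follows the same line. Hypothesis 1 is that "participants who receive the SFBI will decrease their substance use patterns and risk-level use of alcohol", with no comparator, and Hypothesis 2 concerns change between baseline and follow-ups in SFBI recipients. Superiority over usual care is a separate third hypothesis, answered under Objective 3 by a mixed ANOVA with group and time and by Fisher exact tests.

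Two design features bear on this. Under Recruitment, "participants must have an ASSIST score of 11 or higher for alcohol and a score of 4 or higher for other substances". Under Data Collection, every eligible person receives 10 to 15 minutes of counselling and a brochure before consent, and the baseline instruments come after that. No section labels Objectives 1 and 2 as descriptive or warns that change in one arm is not an effect of treatment.

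**The concern.** A paired test in one arm asks whether the mean moved. It cannot say why. In this design at least five things besides the SFBI can move it:

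- the usual-care counselling already given to everyone, which is also the comparator;
- natural course;
- four rounds of assessment;
- attrition, planned at 40%;
- regression to the mean, because entry depends on a screening score at or above a cut-off.

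The control arm, followed at the same visits, exists to separate what is common to both arms from what the SFBI adds. Objectives 1 and 2 leave it out and still name the result a treatment effect. If the trial is analysed as written, two hypotheses about the SFBI could be declared confirmed beside a null randomised comparison. The Discussion expects the result to inform adoption into routine care and public policy, so readers would have to choose between two conflicting statements about efficacy.

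**Working it through.** **1. The plan's own figure.** Inputs from Sample Size: f = 0.12, 80% power, 5% significance, within-between interaction. Two groups (k = 2) and four times (m = 4) come from Objective 3. The article gives no correlation; 0.5 with sphericity is assumed.

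- λ = f²·N·m/(1 − ρ) = 0.0144 × 96 × 4/0.5 = 11.06
- df = (k − 1)(m − 1) = 3 and (N − k)(m − 1) = 94 × 3 = 282
- Power at N = 96 is 0.800
- Attrition: 96/(1 − 0.40) = 160

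Both stated figures reproduce. The trial was sized for the between-group interaction, not for change within an arm.

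**2. One-arm test when the SFBI adds nothing.** Suppose both arms improve by the same d SD, whatever the cause. For a paired t test, dz = d/√(2(1 − ρ)). With assumed ρ = 0.5, dz = d and the noncentrality is d√n. Retained per arm: 96/2 = 48 from the 160, or 320/2 × 0.6 = 96 from the 320. Two-sided 5% level, one visit.

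| Common improvement | n = 48: noncentrality, P(significant) | n = 96: noncentrality, P(significant) |
|---|---|---|
| 0.2 SD | 1.39, 27% | 1.96, 49% |
| 0.3 SD | 2.08, 53% | 2.94, 83% |
| 0.4 SD | 2.77, 77% | 3.92, 97% |
| 0.5 SD | 3.46, 92% | 4.90, 99.8% |

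The true difference between arms is zero in every row, so a between-arm test of change rejects at its nominal 5%.

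**3. How much regression to the mean could contribute.** Selection is on the screening ASSIST, but change runs from a later baseline, so part of the regression may already have happened by then. Simulation with no effect in either arm, the top 5% to 20% selected and 48 per arm gives:

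- *Baseline is itself the selecting value:* one-arm test significant in 99.8% to 100%.
- *Baseline two weeks after screening* (variance assumed 50% stable trait, 30% state with a two-month e-fold decay, 20% noise): 43% to 74% at 3 months and 61% to 91% at 9 months.
- *Screening and baseline share only the stable trait:* about 5% per test.

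The between-arm test rejected in 4.0% to 5.9% throughout (48 and 96 per arm).

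**4. McNemar test with a re-measured baseline.** Assumptions: normal scores, no effect, top 10% or 20% selected, n = 48, the same cut-off at each time, exact test, rejection towards improvement, one visit.

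- All three correlations 0.7, or all 0.9: about 1%. Improving and worsening pairs balance, for example 7.9 against 7.9 on average (top 20%, correlation 0.7).
- Screening-baseline 0.8, the others 0.7: about 11% to 13%.
- Screening-baseline 0.9, the others 0.7: about 49% to 62%.
- Selecting score used as baseline, correlation with follow-up 0.7: about 100%.

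The document gives none of these correlations, so it does not fix a place in this range.

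**The case against.** The strongest defence is that the randomised comparison is intact. The general objective is to do better than usual care, the design is a superiority trial, the sample size serves the group-by-time interaction, and the P<.05 criterion for inference is stated for Objective 3 only. Hypotheses 1 and 2 say only that SFBI recipients will improve, and a paired test addresses that literal statement. Objective 3 already gives mean change with CI in both arms for the TOP, PHQ-9 and GAD-7. All of this stands. It means the trial does not give up its control arm. It does not cure the wording of Objectives 1 and 2, which ask whether the SFBI reduces use and call the one-arm result a treatment effect.

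A reader might go further and infer that regression to the mean will almost surely confirm Hypotheses 1 and 2, or that the McNemar test can move in only one direction because everyone enters at intermediate or high risk. The documents do not support that. Entry is on the screening ASSIST, baseline is measured again after counselling and consent, and the McNemar test is tied to categorical items of the TOP. Some participants may be below a cut-off at baseline, so pairs can change in both directions. The PHQ-9 and the readiness scales are not selection variables, so regression reaches them only through correlation with use. Nor does the text say that one-arm change will be reported as efficacy; it permits that reading.

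**Conclusion.** Wrong as written, in the attribution. A before-after test in the SFBI arm is named a test of treatment effect under causally worded objectives, and it would mislead whenever both arms improve alike. The 53% to 92% (48 per arm) and 83% to 99.8% (96 per arm) are illustrations: they rest on an assumed correlation of 0.5 and an assumed common improvement of 0.3 to 0.5 SD, neither of which is in the document. The share due to regression to the mean cannot be determined, and the conclusion does not depend on it, because counselling given to all, natural course, repeated assessment and attrition are enough to defeat the attribution. The randomised comparison in Objective 3 and the sample size are unaffected.

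**What to change.** - Reword Objectives 1 and 2, and the matching hypotheses, as descriptions of change in the SFBI arm. Remove the causal verb and the treatment-effect phrase.
- Report within-arm change with CIs at 3, 6 and 9 months beside the same figures for the control arm. Objective 3 already provides these for the TOP and PHQ-9.
- State that within-arm ANOVA, Wilcoxon and McNemar results, if kept at all, are not evidence of efficacy.
- State that every efficacy conclusion comes from the between-group contrasts of Objective 3.

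The cost is the wording of two objectives, two hypotheses and their analysis paragraphs. No extra data, participants or sample-size work are needed. The article reports that no analyses have been conducted, so the change can still be made before results are known.

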**Methods:**

We will conduct a randomized controlled clinical trial (ClinicalTrials.gov registration pending) comparing a 3-session SFBI (experimental group) with a single session of brief counselling as usual care (control group) in primary care. Interventions will be delivered in person by a psychologist or social worker. A total of 320 participants are expected to be recruited during preventive routine checkups using the Alcohol, Smoking, and Substance Involvement Screening Test. Participants reporting intermediate- to high-risk substance use on this screening tool will be randomly assigned to each group. Research assistants will administer instruments at baseline and at 3-, 6-, and 9-month follow-ups and will be blinded to the assigned treatments. The primary outcome assessed will be substance use patterns, while secondary outcomes include background information, depressive symptoms, anxiety symptoms, and motivation for treatment. Statistical analyses, including *t* tests, ANOVA, and Fisher exact tests will be conducted depending on variable type and normality. A qualitative component to assess acceptability and pertinence will include focus groups with participants and practitioners, followed by a content analysis.

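### The plan analyses change in the motivation scales after baseline, but Table 1 schedules that form at baseline only and contradicts the text above it

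*Protocol article*

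**What the plan says.** **Motivation.** The Abstract states that "secondary outcomes include background information, depressive symptoms, anxiety symptoms, and motivation for treatment". For the experimental arm, Specific Objective 2 plans the following at each follow-up: "The change in the PHQ-9 questionnaire score and the desire for help and treatment-readiness scales will be calculated", then mean changes with confidence intervals and a repeated-measures ANOVA on each score.

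The schedule is given under Focus Group Guides in the Instruments section. The text there includes the "desire for help and treatment readiness" form in its list of quantitative instruments and continues: "Following the informed consent procedures, the instruments will be administered on 4 occasions (Table 1". In Table 1 itself, the row for this form has one tick, under baseline. The section on the Motivation and Treatment Needs Scale describes two subscales with 14 items in total and gives no timing.

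**Other entries in Table 1.** Of ASSIST the text says: "It is one of the main dependent variables of the study and will be administered at baseline and follow-ups". Table 1 has no row for it. Background information is to be collected "partially (employment status and county of residence) at the 3- and 6-month follow-up", but Table 1 ticks it at baseline and 9 months only.

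**Anxiety.** Under Specific Objective 3, "the change in the GAD-7 score will be calculated for individuals in both experimental and control groups", with a mean and confidence interval. No test between arms is named for it. For depression the same paragraph says: "Similarly, mean PHQ-9 scores will be compared between the two groups using a mixed ANOVA".

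**The concern.** A change score needs a baseline value and at least one later value from the same person. A form given once supplies no change, and a repeated-measures ANOVA has nothing to repeat. If sites work from Table 1, a stated analysis of a named secondary outcome has no data behind it.

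This differs from most gaps in a condensed protocol because an analysis plan written later cannot restore follow-up data that were never collected. Multiple imputation, the article's method for missing data, is no remedy for a variable unobserved in everyone at every follow-up. Timing matters too: recruitment began in February 2025, and the article reports 73 people enrolled and 23 dropped out.

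The GAD-7 point is smaller. Specific Objective 3 and the third hypothesis treat mental health symptoms as one domain, yet only one of the two symptom scales has a named between-group analysis. That leaves it unclear whether, and how, anxiety will be tested.

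**Working it through.** The plan gives no figure to reproduce on this point, and the sample size does not depend on it. The check sets the passages side by side and counts occasions.

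**Step 1: the motivation form.**

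| Source | Occasions for the form | Follow-up values |
|---|---|---|
| Analysis Plan, Specific Objective 2 | baseline, 3, 6 and 9 months (implied by the change scores) | 3 |
| Text introducing Table 1 | 4 | 4 − 1 = 3 |
| Table 1 | 1 (baseline) | 1 − 1 = 0 |
| Motivation and Treatment Needs Scale section | not stated | not stated |

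Computable change scores equal the number of follow-up values. Under Table 1 that is 0 of 3; under the text it is 3 of 3. Two sources imply repeated collection, one implies single collection, and the section that could decide is silent. The sentence giving four occasions cites Table 1, so it offers no independent authority.

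**Step 2: is Table 1 reliable elsewhere?**

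| Instrument | Text | Table 1 |
|---|---|---|
| ASSIST | baseline and follow-ups | no row |
| Background information | complete at baseline and 9 months, partial at 3 and 6 months | baseline and 9 months |
| TOP, PHQ-9, GAD-7 | baseline and follow-ups | all four visits |

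Table 1 agrees with the text for three instruments and falls short of it for two besides the motivation form. It cannot be presumed correct where it conflicts with the text.

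**Step 3: burden of repeating the form.** 14 items × 3 follow-ups = 42 further item responses per participant. The article estimates 25 minutes for administering one set of instruments.

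**Step 4: the two symptom scales under Specific Objective 3.**

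| Item | PHQ-9 | GAD-7 |
|---|---|---|
| Visits with data (Table 1) | 4 | 4 |
| Mean change with CI, each arm | yes | yes |
| Named between-group analysis | mixed ANOVA, group by time | none |
| Fallback if not normal | Friedman-aligned ranks test | none |

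The data are the same in kind and timing. Only the named comparison differs.

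**The case against.** The strongest reply is that Table 1 may simply be wrong. The text says four occasions, the analysis assumes four, and the table is incomplete for two other instruments. On that reading the form is being repeated and nothing is lost. This stands as far as it goes: a reader might infer that motivation data will be absent at follow-up, and the documents do not prove it. They prove a contradiction. That still needs settling, because staff may work from either source.

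The stakes are also limited. Motivation appears in no specific objective and no hypothesis, and its change is analysed in the experimental arm only. No conclusion between arms rests on it. That is fair and keeps the point below the primary outcome.

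On GAD-7, a reader might infer that the arms cannot be compared on anxiety, or that the plan means to compare two within-arm intervals. Neither is supported. GAD-7 is collected in both arms at every visit, Specific Objective 3 is a between-arm objective, and the article never proposes to judge the arms by inspecting separate intervals. The Abstract also says tests will be chosen by variable type and normality, and an unseen analysis plan may name the test. What remains is an unexplained asymmetry in a paragraph that otherwise specifies its analyses test by test.

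A reader might likewise infer that consequences of use cannot be answered. They are an objective and a hypothesis but are not in the Abstract's list of secondary outcomes. TOP, whose sections include offending behaviour and physical and psychological health, is given at all four visits. Which TOP items represent consequences is missing detail that an analysis plan commonly supplies.

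**Conclusion.** The point holds as an internal contradiction. Specific Objective 2 plans three post-baseline change analyses of the motivation scales. Table 1 supports none of them, and the text introducing Table 1 supports all three. If Table 1 governs, that analysis of a named secondary outcome cannot be done, and data for visits already completed may be unrecoverable. If the text governs, the table needs correcting and no data are lost. The documents do not say which applies, or how many follow-up visits have taken place.

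This assumes that the Table 1 row was read correctly. It looks intact: the ticks in neighbouring rows fall in sensible columns.

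The secondary point is the lack of a named between-group analysis for GAD-7 beside the one for PHQ-9. It is a gap in specification that wording can close. The documents do not support saying that anxiety or consequences of use cannot be compared between arms.

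**What to change.** First check what the REDCap forms actually collect at 3, 6 and 9 months. Then make Table 1, the sentence introducing it and Specific Objective 2 agree, in one of two ways:

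1. Schedule the 14-item form at the three follow-ups and tick it in Table 1. The cost is 42 item responses per participant. If the form has not been repeated so far, it will be missing for visits already done, and the report should say so.
2. Keep the form at baseline only, delete its change analysis, and describe motivation as a baseline variable instead of a secondary outcome. This adds no burden for participants and gives up the change question.

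In the same revision, add an ASSIST row to Table 1 and mark the partial background collection at 3 and 6 months.

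For anxiety, state that GAD-7 will be compared between arms with the same model and fallback as PHQ-9. Also state which TOP items represent consequences of use and how they will be compared. Both are wording changes, to be made before any outcome data are analysed; the article reports that no analyses have yet been conducted.
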